#### Data management

This RCT will comply with the principles outlined in the Declaration of Helsinki [69]. Written informed consent will be obtained from all participants, and their personal data and consent forms will be stored in locked units at the outpatient clinic for archival purposes. Each participant will be assigned a unique ID number to maintain anonymity, and all data collected on the computer system will be based only on this ID number. The document files, including the ID number data and participant awareness, will be kept separate from the study information files and the consent forms. Only the principal investigator and team members of the study will have access to the participant ID number list and information sheets.

Clinical data will be collected and documented by trained research assessors in our outpatient clinic. Clinical data will be recorded on case report forms and then entered electronically into a secure computer system. This study adheres to accepted clinical practices to safeguard patients’ rights and benefits [69]. All data collected will be validated against the source documents and All data collected will be validated against the source documents and The data will be kept at health Centre for five years after the data collection. All raw data required to replicate the results of your study. Participants will be informed that they may withdraw their consent at any time during the study and that their medical care or legal rights will not be affected.

The Trial Steering Group and independent Data Monitoring and Ethics Committee will meet to review conduct throughout the trial period, once every two months, or as needed based on any reported adverse event. Safety monitoring will begin at the start of trial recruitment. The committee will provide a report detailing all adverse events and protocol deviations, which will be notified and updated in the clinical trial registry. This will be a small study; therefore, there will be no requirement for an interim analysis or stopping guidelines.

### Statistical analysis

The sample size has been estimated for the primary outcome of pain intensity (VAS), with emphasis on the proportion (%) of patients with improved CLBP on the VAS. The minimal important change in VAS is reported to be 15 mm [70]. Accordingly, we expect a minimal difference of 20% between the intervention groups in the proportion of patients with an improved VAS score (at least 15 mm) [27]. To detect a difference in main effects (i.e., PNE plus NMS vs NMS), the sample size calculation using G*Power software and like previous studies in the field of PNE (30), with an effect size difference of 0.25, an alpha value of 0.05 (two-sided test), and power (1 × b) 0.80, results in a required total sample size of 60 participants (30 patients per group). Assuming a dropout rate of 20%, we will enroll 30 patients per group.

A 2 × 2 variance analysis (treatment group × time) will be conducted using a mixed-model analysis design. The percentage change will be calculated for each variable compared to the baseline. The effect size (ES) using partial eta squared (ηp2) will be calculated to measure the clinical meaningfulness [71]. For ITT analyses, group means will replace missing data during the post-test. There will be no additional analyses (e.g., subgroup and adjusted analyses). All data analyses will be conducted using the SPSS software version 26 (IBM Corp., Armonk, NY, USA) at an alpha level of 0.05.

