However, there are several limitations to this study. The sample size, although statistically adequate, may limit the generalizability of the results to the broader CLBP population. Further studies with larger sample sizes are required to confirm our future findings. Another limitation is the monocentric design, as the study will be conducted within a single outpatient healthcare setting and will consider patients with CLBP (not recurrent LBP) [30] exclusively from Iran, impacting the external validity of the findings. Additionally, the lack of a validated Persian version of the Central Sensitization Inventory [22,32] will hinder exploration of the relationship between pain improvement and central sensitization. Furthermore, we have considered patient-reported outcomes (PROs) as primary and secondary outcomes. Although PROs are commonly used in RCTs, they are prone to limitations, such as response bias, recall bias, and the subjective nature of self-reported data [73]. Finally, excluding individuals above the age of 60 and below 30 years old from the study will restrict the applicability of our findings to these specific age groups. Further research should incorporate a wider range of age groups and investigate long-term outcomes to better understand the effectiveness of the interventions.

In conclusion, our RCT can contribute to advancing the management of CLBP and optimizing patient care, thus providing new insights to the rehabilitation field.

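### The 80% power and N = 60 are not linked to the 20-point responder difference that frames them; 30 per arm gives about 34–49% power for it at assumed control rates of 10–70%

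*Protocol article*

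**What the plan says.** The sample-size paragraph (protocol article, Statistical analysis) sizes the trial on VAS pain, "with emphasis on the proportion (%) of patients with improved CLBP on the VAS". It sets the threshold: "The minimal important change in VAS is reported to be 15 mm". It then gives the target: "we expect a minimal difference of 20% between the intervention groups in the proportion of patients with an improved VAS score".

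The next sentence changes to a G*Power run for a difference in main effects between the arms, "with an effect size difference of 0.25", "an alpha value of 0.05 (two-sided test" and power 0.80. It reports that this "results in a required total sample size of 60 participants (30 patients per group". A 20% dropout is assumed, yet enrolment stays at 30 per group.

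The planned analysis in the same section is a 2 × 2 group-by-time mixed ANOVA on the scores. The Outcomes variables section lists three measurement times. The limitations part of the Discussion comments: "The sample size, although statistically adequate, may limit the generalizability".

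**The concern.** The paragraph contains two targets, a 20-point difference in responder proportions and an effect size of 0.25, and nothing converts one into the other. The paragraph opens on the responder difference and closes on 80% power, so a reader will join the two. The planned test uses means, so it does not test the responder difference at all.

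What is at stake is interpretation. If a 20-point gain is real, a trial of this size would more often than not miss it in a comparison of proportions (at control rates of 10–70%). A null result could then be read as evidence that adding PNE gives no such gain, and the remark on adequacy in the Discussion encourages that reading.

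**Working it through.** **Inputs from the document:** 20-point difference (read as absolute), two-sided alpha 0.05, power 0.80, effect size 0.25 with no metric named, 1:1 allocation, 30 per arm, 20% dropout (24 completers per arm). **Assumed, because not given:** control responder rate, effect-size metric (Cohen's f unless noted), correlation r between repeated VAS scores.

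**1. Can 0.25 reproduce 60?** Noncentral F for 2 groups and m times, with noncentrality:
- group main effect: λ = N f² m / [1 + (m − 1) r]
- group × time: λ = N f² m / (1 − r)

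| Test, f = 0.25 | r | Total N for 80% | Power at N = 60 |
|---|---|---|---|
| One measurement | – | 128 | 48% |
| Main effect, m = 2 | 0 | 66 | 77% |
| Main effect, m = 2 | 0.5 | 98 | 59% |
| Main effect, m = 3 | 0.19 | 60 | 80% |
| Main effect, m = 3 | 0.5 | 86 | 65% |
| Group × time, m = 2 | 0.1 | 60 | 81% |
| Group × time, m = 2 | 0.5 | 34 | 97% |

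For the main effect with m = 2, N rises with r from 66, so no non-negative correlation gives 60. Read instead as a standardised mean difference, 0.25 gives power of 16% at 30 per arm.

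**2. Power for the responder difference.** With p̄ = (p₁ + p₂)/2:
- power = Φ{ [0.20 √n − 1.96 √(2p̄(1 − p̄))] / √(p₁(1 − p₁) + p₂(1 − p₂)) }
- n per arm = [1.96 √(2p̄(1 − p̄)) + 0.8416 √(p₁(1 − p₁) + p₂(1 − p₂))]² / 0.20²

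Example, 40% v 60%, n = 30: (1.0954 − 1.3859)/0.6928 = −0.419, so power is 34%. Required n = (1.3859 + 0.5831)²/0.04 = 96.9, so 97 per arm.

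| Control v PNE | Power, 30 per arm | Power, 24 per arm | n per arm for 80% |
|---|---|---|---|
| 0 v 20% (limit) | 75% | 64% | 35 |
| 5 v 25% | 59% | 49% | 49 |
| 10 v 30% | 49% | 41% | 62 |
| 20 v 40% | 39% | 32% | 82 |
| 30 v 50% | 35% | 29% | 93 |
| 40 v 60% | 34% | 28% | 97 |

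Higher control rates mirror these (70 v 90% equals 10 v 30%). Exact enumeration for control rates of 10–70% gives 35–50% for the chi-square test and 26–37% for Fisher's test. If the 20% were relative (50% v 60%), power would be about 12%.

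**3. What 60 can detect in the planned model.** With two times, the group × time F test is the square of a two-sample t test on the change score, with noncentrality d √(n/2), where d is in SDs of change.
- n = 30: 0.74 × √15 = 2.87 on 58 df gives 80% power.
- n = 24: 0.83 × √12 = 2.88 on 46 df gives 80% power.

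SD of change = SD of VAS × √(2(1 − r)), so the two SDs are equal at r = 0.5. The article's 1.5 cm MCID is detectable with 80% power only if the SD of change is at most 1.5/0.74 = 2.0 cm, or 1.5/0.83 = 1.8 cm with 24 per arm. No SD is given.

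This also explains the 97% in step 1. For group × time at r = 0.5, λ = 60 × 0.0625 × 2/0.5 = 15. Setting 15 d² = 15 gives d = 1.0, so f = 0.25 there means a full SD of change.

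**The case against.** The strongest reply is that the stated 80% is attached to the 0.25 and not to the responder difference, which the text only emphasises. On that view the plan has two unlinked targets, not a wrong power for the figure that was computed. That is fair, and it is why the point concerns the missing link and what a reader will take from it.

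A reader might go further and infer that 60 cannot come from 0.25. The documents do not support that. It comes out exactly for group × time with two times at r of about 0.1, and for the main effect with three times at r of about 0.19. The latter fits both the main-effects wording and the three assessments, though not the 2 × 2 model. The article is condensed, and the correlation and test family may be stated in the full protocol.

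A reader might also infer that the trial is underpowered for its own analysis. That does not follow either: the group × time test at f = 0.25 and r = 0.5 has 97% power at N = 60.

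It is also true that no responder analysis is planned, that the article calls the study small and asks for larger ones, and that the adequacy remark is made in passing. These points limit the harm. They do not link 20% to 0.25.

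**Conclusion.** The point holds in this form. The paragraph frames the size on a 20-point responder difference and reports 80% power, but 30 per arm does not give 80% for that difference at any control rate. Power is about 34–49% for assumed control rates of 10–70%, at most about 75% at the extremes, and 28–41% over the 10–70% range with 24 completers per arm. This rests on reading 20% as an absolute difference; a relative reading is worse.

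The effect size of 0.25 is a lesser matter. For the named main effect in the stated 2 × 2 model, no non-negative correlation gives 60; other tests give it at low correlations that the article does not state. That is mainly a matter of unstated inputs. Nothing here shows that 60 is too few for the group × time comparison, because that depends on an SD and a correlation the article does not provide.

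**What to change.** Keep 60 patients and rewrite the sample-size paragraph.

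- Remove the 20-point responder target from the justification, or state its true power together with the assumed control rate.
- Name the test that is powered (the group × time contrast that will be run), the effect-size metric, the number of times and the correlation.
- State that 30 per arm detects about 0.74 SD of the VAS change score with 80% power (equal to 0.74 SD of VAS if r = 0.5), or 0.83 SD with 24 per arm after the plan's own 20% dropout. Set this against the 1.5 cm MCID using a stated SD. Use these unadjusted figures, since the section rules out adjusted analyses.
- Delete the claim in the Discussion that the size is statistically adequate.

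The cost is one rewritten paragraph, one deleted phrase and a less favourable stated power. No extra patients are needed.

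### The trial is sized for an arm main effect, its 2 × 2 ANOVA names neither the deciding test nor the two time points, and baseline adjustment is ruled out

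*Protocol article*

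**What the plan says.** Three sentences in the protocol article's Statistical analysis section bear on this.

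- **Sample size.** The calculation is made "To detect a difference in main effects (i.e., PNE plus NMS vs NMS", "with an effect size difference of 0.25, an alpha value of 0.05 (two-sided test", "and power (1 × b) 0.80", and it "results in a required total sample size of 60 participants (30 patients per group". The arm main effect is the only contrast named.
- **Model.** "A 2 × 2 variance analysis (treatment group × time) will be conducted using a mixed-model analysis design". No deciding F test is named, and the two time levels are not identified.
- **Exclusion.** "There will be no additional analyses (e.g., subgroup and adjusted analyses".

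Elsewhere, Outcomes variables fixes three assessments: before treatment, at 8 weeks and at 6 months. Table 1 heads one pre-test and one post-test column, and the missing-data sentence in Statistical analysis speaks of a single post-test. Table 1 also shows that VAS, ODI, FABQ, PSEQ and TSK are all measured at baseline.

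**The concern.** In a group-by-time ANOVA with baseline as one time level, the arm main effect averages the baseline difference, which randomisation makes zero in expectation, with the post-treatment difference. A test of that effect would look for a diluted version of the treatment effect.

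The interaction in a 2 × 2 layout avoids the dilution because it is the between-arm comparison of change scores. It is still less precise than a comparison adjusted for baseline. The plan goes further than leaving adjustment unmentioned: it rules it out, although each outcome's own baseline is already collected.

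At stake are the power of a 60-patient trial and a primary result that could be read from either of two F tests with different meanings.

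**Working it through.** **Inputs from the article.** 30 per arm, two-sided alpha 0.05, effect size 0.25 (type not stated), power 0.80, dropout 20%, and a VAS MCID of 1.5 cm (Primary outcome, Pain).

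**Assumptions.** The article gives no SD and no pre-post correlation r. I take SD 1.5, 2.0 and 2.5 cm and r from 0.2 to 0.8, with equal variance at each visit. The 1.5 cm MCID serves as an illustrative between-arm difference.

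**1. The plan's own figure.** I read 0.25 as Cohen's f and use the noncentral F for two arms and two times.
- Arm main effect, λ = N·2·f²/(1+r): the total N for 80% power is 66, 84, 98 and 116 at r = 0, 0.3, 0.5 and 0.8. N = 60 is not enough at any r ≥ 0; at r = 0.5 its power is 59%.
- Interaction, λ = N·2·f²/(1−r): N is 60 at r = 0.1 and 34 at r = 0.5.

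The stated 60 is therefore not reproduced for a two-level arm main effect, and it matches the interaction only at about r = 0.1. The number does not settle which test was meant.

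**2. What each test estimates.** Let δ be the post-treatment difference, with equal expected baselines and the same δ at both follow-up visits.
- Main effect, baseline and week 8: (0 + δ)/2 = δ/2.
- Main effect, all three visits: (0 + δ + δ)/3 = 2δ/3.
- Main effect, week 8 and month 6: (δ + δ)/2 = δ.
- Interaction (baseline and week 8) and ANCOVA: δ.

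A 10,000-run simulation with a true effect of 0.75 SD, r = 0.5 and baseline plus one post value gave mean estimates of 0.378 (main effect), 0.748 (change) and 0.750 (ANCOVA).

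**3. Precision.** With d = δ/SD, the standardised effects are:
- main effect: (d/2)/√((1+r)/2)
- interaction: d/√(2(1−r))
- ANCOVA: d/√(1−r²)

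The variance ratio of change score to ANCOVA is 2(1−r)/(1−r²) = 2/(1+r). This is 1.67, 1.54, 1.33, 1.18 and 1.11 at r = 0.2, 0.3, 0.5, 0.7 and 0.8, and it exceeds 1 for every r below 1.

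**4. Power (noncentral t, noncentrality = standardised effect × √(n/2)).** At SD 2.0, d = 1.5/2.0 = 0.75. With r = 0.5 the standardised effects are 0.433, 0.750 and 0.866. With n = 30, √15 = 3.873, so the noncentralities are 1.68, 2.90 and 3.35.

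| SD (cm), r = 0.5, 30 per arm | Main effect | Interaction | ANCOVA |
|---|---|---|---|
| 1.5 | 59% | 97% | 99% |
| 2.0 | 38% | 81% | 91% |
| 2.5 | 26% | 63% | 75% |

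Varying r at SD 2.0 and 30 per arm:

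| r | Main effect | Interaction | ANCOVA |
|---|---|---|---|
| 0.2 | 45% | 62% | 83% |
| 0.3 | 43% | 68% | 85% |
| 0.7 | 34% | 96% | 98% |
| 0.8 | 33% | 99% | 99.7% |

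The article states: "Assuming a dropout rate of 20%, we will enroll 30 patients per group". After 20% loss, 24 per arm remain (30 × 0.8). At SD 2.0 and r = 0.5, power is then 31%, 72% and 84%.

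**The case against.** A reader might infer that the plan will test the arm main effect and so will certainly halve the treatment effect. The article does not support that. The main-effects wording stands only in the sample-size sentence, where the parenthesis may mean no more than the comparison between arms. The analysis sentence names no F test, and the next one, on percentage change from baseline, fits an interest in change. The factor of one half also needs the time levels to be baseline and week 8. The single post-test makes that the likeliest reading, but the three assessments leave other readings open.

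If the interaction decides, the analysis is a valid, unbiased randomised comparison that already uses baseline. What remains is then a loss of efficiency, modest at high r: 96% against 98% power at r = 0.7 and SD 2.0.

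The power figures rest on assumed SDs. At SD 1.5 even the main effect has 59% power, so it cannot be said without qualification that a real effect would probably be missed. The VAS entry threshold of 5 may also lower r. That would shrink ANCOVA's gain over a post-only comparison to about 4% in variance at r = 0.2 (1 − r² = 0.96), but it would widen its gain over the change score.

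All of this stands and makes the dilution conditional. It does not remove the unnamed test and time points, or the stated exclusion of adjustment. The exclusion cannot be treated as a detail left to a statistical analysis plan, because an analysis plan that adjusted for baseline would contradict the article.

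**Conclusion.** The point holds in conditional form. The plan sizes the trial for an arm main effect, leaves the deciding test and the two time levels open, and rules out adjusted analyses.

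- **Dilution (moderate confidence).** The estimate is δ/2 if the main effect is tested over baseline and week 8, and 2δ/3 over all three visits. There is none over week 8 and month 6, or if the interaction is tested.
- **Lost precision (high confidence).** Even on the favourable reading, in which the interaction over baseline and week 8 decides, its variance is 2/(1+r) times that of ANCOVA. The direction does not depend on the r assumed. At r = 0.5 and 30 per arm, the interaction loses about 2, 9 and 12 percentage points of power at SD 1.5, 2.0 and 2.5 cm.

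The size in power terms rests on the assumed SD and r and on a 1.5 cm between-arm difference. The plan should be changed on this point.

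**What to change.** 1. Name the primary contrast: the week-8 between-arm difference in VAS adjusted for baseline VAS. Estimate it by ANCOVA, or by a mixed model for week 8 and month 6 with baseline and baseline × time as covariates.
2. Use the same form for each secondary outcome, with its own baseline as covariate.
3. Reword the exclusion of adjusted analyses so that it permits baseline adjustment.
4. Replace the main-effects wording in the sample-size sentence with this contrast, and restate the sample size and power for it with the assumed SD and correlation given.

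No new data are needed, since every baseline is already collected. The cost is rewording and one recalculation. Trial status reports recruitment under way, so the change should be recorded and dated before outcome data are examined.

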### Setting and participants

Before starting the project, all patients will complete and sign an informed consent form based on the latest revision of the Declaration of Helsinki [38]. The population considered for this research will comprise Persian patients aged 30–60 years with CLBP. Participants will be informed about this study and how to register through advertisements in physical therapy centres, research group networks, and social media. A physiotherapist and a sports injury specialist will recruit and register patients in a physiotherapy clinic. Then, on a certain date, the registration of all patients in the health centre and human performance laboratory of Kharazmi University will be completed in person, and qualified people will be included in the study. Among the participants, 60 will be randomly divided into Group 1, Experimental-PNE plus NMS (n = 30) and Group 2 Control-NMS (n = 30). Participants will be informed that they are free to withdraw consent at any time during the study.

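### The sample-size text assumes 20% dropout but enrols exactly the 60 patients it calls required, so the allowance is not applied; on the plan's own premise, power falls from 80% to about 70%

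*Protocol article*

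**What the plan says.** Everything on sample size stands in one paragraph of the protocol article, under Statistical analysis. The calculation is aimed at the group comparison ("To detect a difference in main effects (i.e., PNE plus NMS vs NMS")), "with an effect size difference of 0.25", "an alpha value of 0.05 (two-sided test") "and power (1 × b) 0.80". The paragraph reports that this "results in a required total sample size of 60 participants (30 patients per group"). The sentence after it is "Assuming a dropout rate of 20%, we will enroll 30 patients per group".

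The other sections agree on the number randomised. Setting and participants states that "60 will be randomly divided into Group 1, Experimental-PNE plus NMS (n = 30) and Group 2 Control-NMS (n = 30"), and the Abstract and Randomization sections give the same 30 and 30. No section gives a smaller evaluable target or says that 60 already contains an allowance for dropout. The Statistical analysis section also says that, for the intention-to-treat analyses, missing post-test values will be filled in with group means.

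**The concern.** A dropout allowance turns the number needed for analysis into a larger number to enrol. Here the two numbers are identical, although the assumed loss is one patient in five. As written, the two sentences cannot both be right: either 60 must be analysed and more than 60 must be enrolled, or 60 is the enrolled number and fewer than 60 are required for analysis.

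This paragraph is the only sample-size justification for the primary outcome, and the Discussion calls the sample statistically adequate. If the first sentence is taken at its word, the risk of missing the effect the trial was sized for rises from 20% to about 30% under the plan's own attrition. A null result would then be read against a power that the trial did not have. Group-mean replacement makes this harder to see, because the analysed data set will again show 60 rows.

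**Working it through.** **Inputs, all from the Statistical analysis section:** required total 60 (30 per group), power 0.80, two-sided alpha 0.05, dropout 20%, enrolled 30 per group. The effect size is given as 0.25 without naming its metric. The correlation between repeated measurements is not given.

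**Step 1. Can the 60 be reproduced?** Not from the stated inputs alone. Totals needed for 80% power:

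| Reading | Total N |
|---|---|
| One-way ANOVA, f = 0.25 | 128 |
| Repeated measures, between-group effect, f = 0.25, assumed correlation 0.5 | 98 (2 measurements), 86 (3 measurements) |
| Repeated measures, group × time interaction, f = 0.25, assumed correlation 0.5 | 34 (2 measurements), 28 (3 measurements) |
| Two-sample comparison, d = 0.25 | about 504 |
| 20-point responder difference, control rate assumed 0.10 to 0.70 | 124 to 194 |

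A figure near 60 appears only with a low correlation that the article does not state. The interaction with 2 measurements and correlation 0.1 gives 60. The between-group effect with 3 measurements and correlation 0.2 gives 62. What follows therefore takes the plan's statement that 60 gives 80% power as a premise.

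**Step 2. Dropout arithmetic.**
- Expected evaluable if 60 are enrolled: 60 × (1 − 0.20) = 48, or 24 per group.
- Enrolment that keeps 60 evaluable: 60/(1 − 0.20) = 75. Equal arms need 38 each, 76 in total.
- Under the other reading, an analysed requirement of 48 inflates to 48/0.8 = 60.

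**Step 3. Power at 48, given 80% at 60.** Solve for the standardised difference that has exactly 80% power at 30 per group, then evaluate it at 24 per group.
- Noncentral t, noncentrality d × √(n/2): 80% at n = 30 (58 df) gives d = 0.736. At n = 24 (46 df) the noncentrality is 0.736 × √12 = 2.55 and power is 0.704.
- Normal approximation: d = 0.723, power 0.707 at 24 per group.
- The two repeated-measures variants that come close to 60 give the same picture. The interaction (correlation 0.1) goes from 0.810 at 60 to 0.715 at 48. The between-group effect (correlation 0.2) goes from 0.796 to 0.699.

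The value d = 0.736 is only a device for carrying the 80% premise from 60 to 48. It is not an effect size in the plan.

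**Step 4. Does group-mean replacement recover the loss?** Take a two-group t-test on the post-test with 24 observed and 6 mean-filled values per arm. The filled values leave the group means and the within-group sums of squares unchanged, while the software counts 30 per arm and 58 df. The t statistic is therefore multiplied by √(30/24) × √(58/46) = 1.118 × 1.123 = 1.255. The nominal critical value 2.00 (58 df) corresponds to 2.002/1.255 = 1.594 on the true 46-df scale.
- Under no difference, the test rejects with probability 0.118, not 0.05. A simulation of 40,000 runs gave 0.117.
- At d = 0.736 it rejects with probability 0.83. The complete-case test rejects with probability 0.70 and holds its level (0.049 in the simulation).

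The apparent gain comes from an inflated type I error. No information is recovered.

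**The case against.** The strongest counter-argument is that 48 may have been the calculated requirement and 60 the inflated figure. The numbers fit exactly (48/0.8 = 60), and the dropout sentence, read alone, could be presenting the inflated enrolment. On that reading no power is lost. This cannot be excluded. What weighs against it is that 60 is called the required number, and tied to the calculation, before dropout is mentioned, while 48 appears nowhere. Even if it is what was meant, the required figure is misstated and needs correcting.

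A second objection is that 70% does not come from the plan's inputs. It is obtained by back-solving from 80% at 60, using a t-test rather than the planned mixed analysis. That stands as a limit on what the 70% means. With f = 0.25 and the unstated correlation anywhere from 0 to 0.7, power at 48 ranges from 0.45 to 0.84 for the between-group effect and from 0.67 to above 0.99 for the interaction. A reader might infer that this trial will have 70% power, and the article does not support that. The roughly ten-point drop from a stated 80% does not depend on the t-test, as the two repeated-measures variants show.

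A third objection is that intention-to-treat keeps all 60 in the analysis. It keeps 60 rows, but step 4 shows that the filled values add no information.

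Finally, a full protocol or analysis plan might hold more detail. The point is not an omission, however: the article prints both numbers, and they conflict.

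**Conclusion.** The statement is wrong as written. The plan calls 60 the number required for 80% power, assumes 20% dropout, and enrols 60. Under its own premise that 60 analysed patients give 80%, the expected 48 evaluable patients (24 per group) give about 70% (0.704 to 0.707), and holding 60 evaluable would have needed 75, or 76 with equal arms.

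The contradiction rests on the text alone. The size rests on two assumptions: that 60 analysed gives 80%, which could not be reproduced from the stated 0.25, and that dropout is the stated 20%. Two stronger readings are not supported. One is that the trial's actual power is 70%, since the test and correlation behind 60 are not given. The other is that enrolment must rise to 75, since a restatement resolves the contradiction and 60 may already be the inflated figure. Nor can one say that baseline adjustment would make up the loss: the article gives no baseline to post-test correlation and rules out adjusted analyses.

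**What to change.** Give the evaluable and the enrolled number separately, with the power at each. If 60 is what the calculation returned, wording such as this would do: *60 patients will be randomised; with 20% dropout about 48 are expected to be evaluable, giving about 70% power for the effect for which 60 gives 80%.* If the calculation returned 48, change the required figure to 48 and present 60 as 48/0.8.

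In either case, rerun the power with the G*Power test actually used and report its inputs: the test family, the metric of the 0.25, the number of measurements and the assumed correlation. The 70% should then be replaced by the recomputed value. No back-solved standardised difference should be printed beside the stated 0.25, because readers would then face two effect sizes that do not agree.

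The cost is a sentence or two and possibly a less favourable stated power. No extra patients are needed, and neither the design nor the randomisation changes, so the correction remains feasible with recruitment under way.
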